### Sample size {14}

Because of the potential of notable morbidity, recurrent cSDH is considered both a clinically relevant and methodologically reliable, objective primary trial endpoint.

In one of the largest studies to date, Ban et al. compared a prospective series of 72 patients with cSDH undergoing MMA embolization with a historic standard-of-care group of 469 subjects. The overall risk difference (irrespective of hematoma evacuation) was estimated at 26% (95% CI 21 to 31%) in favor of endovascular management. There is much variability in reported cSDH recurrence risks with either treatment option, and unclarity about the realistic benefit of combined surgical and interventional therapy.

In view of the results of published studies (in particular Ban et al.), we conservatively presume recurrence rates of 30% in the control and 10% in the experimental arm during an observation period of 3 months.

Since our assumptions are subject to uncertainty, we will employ an adaptive design according to O’Brien-Fleming with one planned interim analysis to decide about the further trial progress, and to modify the target sample size if necessary and/or reasonable. For a power of 80% and a total alpha of 5%, data from 138 patients (i.e., 69 per group) are needed to detect a risk difference of 20% by a *z*-test for independent samples. Assuming a drop-out and lost-to-follow-up rate of 10%, we plan to enroll 154 patients (i.e., 77 per treatment arm) unless the interim look prompts any adjustment.

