## Statistical methods

### Statistical methods for primary and secondary outcomes {20a}

The primary outcome, i.e., reduction in cSDH recurrence through the experimental, surgical plus endovascular treatment, compared to surgery alone, will be analyzed using a chi-square fourfold test for independent samples. The two-sided significance level *α* is set at 5% and the power at 80%. Superiority of the experimental intervention over control is assumed, if the resulting *p*-value is below the nominal significance level of 0.00031 at the time of interim analysis (prompting early trial termination), or the nominal significance level of 0.0469 at the time of final analysis.

Secondary categorical outcomes will be investigated by the Cochran-Mantel-Haenszel (CMH), chi-square, or Fisher’s exact test (if one of the cell frequencies is <5). Recurrence-associated complications, complications associated with endovascular embolization, and (serious) adverse events will be expressed as absolute and relative frequencies.

Exploratory analyses will be performed for the distribution of genetic variants and their correlation (by Pearson’s *phi*-coefficient) with factor XIII deficiency (<70%) across the entire cohort without stratification for the type of intervention. The closer the *phi*-coefficient to 1 or -1, the stronger the association (or predisposition) between genetic variants and factor XIII deficiency. Advanced analyses will be performed to study the association between heterozygous, homozygous, and wild type variants, factor XIII activity, and cSDH recurrence.

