### Interim analyses {21b}

The planned interim analysis according to the O’Brien-Fleming design will be conducted after the recruitment of half of the target sample. Given the predicted recruitment speed and rate will be reached on time, the interim analysis will be conducted 12 months after first-patient-in (plus 3 months of follow-up), corresponding to 77 included patients and 69 evaluable data sets. If a statistically significant advantage in the recurrence rate of the experimental group can be demonstrated at the time of the interim analysis with a *p*-value of the chi-squared test of <0.0031, the experimental therapy will be assumed to be superior to the standard of care, leading to premature termination of the study. If the effect size is lower than presumed, a larger sample size and enrolment of additional trial sites must be considered. Investigators will discuss this option together with the funding body and the DSMB. If the likely risk difference between treatments is much smaller than expected and the recalculated sample size exceeds numbers which cannot be achieved, the trial will be terminated for futility. The trial will also be terminated early if the surgery-only control group turns out to be superior to combined management in any case, or if major novel scientific evidence shows any substantial favor of one over the other approach.

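### Two interim efficacy thresholds that differ tenfold (0.00031 and 0.0031) give opposite stopping decisions, and the final level 0.0469 is not the matching O'Brien-Fleming level

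*Protocol article*

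**What the plan says.** All of this is in the protocol article.

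- **Statistical methods {20a}** sets the error rates. Alpha is two-sided and "is set at 5% and the power at 80"%. The thresholds for claiming superiority on the chi-square test are given as "the nominal significance level of 0.00031 at the time of interim analysis (prompting early trial termination), or the nominal significance level of 0.0469"; the second figure applies to the final analysis.
- **Interim analyses {21b}** states the rule for the same look again: early termination follows a p-value "of the chi-squared test of <0.0031, the experimental therapy will be assumed to be superior to the standard of care". It places the look at 77 included patients and 69 evaluable data sets.
- **Sample size {14}** describes an O'Brien-Fleming design "with one planned interim analysis to decide about the further trial progress". It needs 138 evaluable patients and assumes recurrence of 30% in the control arm and 10% in the experimental arm.

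No section says which interim value governs, and the boundary is not specified beyond the name O'Brien-Fleming.

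**The concern.** There is one look, one test and one decision, but two thresholds a factor of ten apart. If the interim p-value falls between them, {21b} ends the trial with a superiority claim and {20a} keeps it recruiting. The choice would then be made with the result in view, which a pre-specified boundary is meant to prevent. A trial stopped on the looser value could be challenged under the stricter one, and the reverse.

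The final level raises a separate, smaller question. Interim and final statistics are correlated because the final data contain the interim data. The nominal final level that exhausts 5% is therefore larger than 5% minus the interim alpha. The figure 0.0469 looks like that plain subtraction.

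**Working it through.** **Inputs.** Two-sided alpha 0.05 ({20a}). One interim at 69 of 138 evaluable patients, so t = 69/138 = 0.5 ({14}, {21b}). Recurrence 30% v 10% ({14}). Allocation 1:1, so 69 evaluable patients split 35/34 or 34/35.

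**1. Which interim value can be reproduced?**

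- Lan-DeMets O'Brien-Fleming-type spending, per side: 2[1 − Φ(z₀.₀₁₂₅/√t)] = 2[1 − Φ(2.2414/0.7071)] = 2[1 − Φ(3.170)] = 0.001525. Two-sided this is 0.00305 (z = 2.96), which rounds to **0.0031**, the value in {21b}.
- Classic O'Brien-Fleming: critical values 2.797 and 1.977, nominal levels 0.0052 and 0.0480.
- 0.00031 corresponds to z = 3.61. No O'Brien-Fleming variant tried at half information gives it.

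**2. Which final level goes with it?** Under the null, the two z-statistics are bivariate normal with correlation √0.5 = 0.707. The overall error is 1 − P(|Z₁| < c₁, |Z₂| < c₂); setting it to 0.05 gives c₂.

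| Interim level | Matching final level |
|---|---|
| 0.0031 (Lan-DeMets) | 0.0490 |
| 0.0052 (classic) | 0.0480 |
| 0.00031 | 0.04995 |

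None is 0.0469, whereas 0.0500 − 0.0031 = 0.0469 exactly.

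**3. Overall two-sided alpha of each pair.**

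| Interim / final | Overall alpha |
|---|---|
| 0.0031 / 0.0469 | 0.0480 |
| 0.00031 / 0.0469 | 0.0469 |
| 0.0031 / 0.0490 | 0.0500 |

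**4. How often do the two interim rules disagree?** Full enumeration of the uncorrected chi-square test, counting crossings in favour of embolization:

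| True rates | Crosses 0.0031 | Crosses 0.00031 | Sections disagree |
|---|---|---|---|
| 30% v 10% | 16.0-17.6% | 3.5-4.4% | 12.5-13.2% |
| 30% v 15% | 5.9-6.4% | 1.0-1.2% | about 5% |
| 30% v 20% | 1.9-2.1% | 0.2-0.3% | about 2% |
| 20% v 20% | 0.1% | <0.01% | about 0.1% |

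The ranges cover the 35/34 and 34/35 splits. Two examples: 12/35 control v 1/34 experimental recurrences gives p = 0.0009, and 14/35 v 2/34 gives p = 0.0008. Both stop the trial under {21b} and continue it under {20a}. With a pooled rate of 20%, the standard error is √(0.16 × (1/35 + 1/34)) = 0.096. The observed difference needed is therefore about 2.958 × 0.096 = 28 points under {21b} and 3.607 × 0.096 = 35 points under {20a}.

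**5. Cost of the strict final level.** By the pooled normal approximation at 69 per arm, power is 83.0% with 0.0031/0.0469 and 83.4% with 0.0031/0.0490. By enumeration at 69 v 69 and 30% v 10%, the chance of a final p-value between 0.0469 and 0.0490 in favour of embolization is 0.2 points.

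**The case against.** The slip can largely be read from the text. The value 0.0031 fits O'Brien-Fleming-type spending at half information and adds to 0.0469 to make exactly 0.05, so 0.00031 is probably one zero too many. That inference is sound, but a stopping rule should not depend on inference, and the suspect figure stands in the section that defines the primary analysis.

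The final level contradicts no other passage, plays no part at the interim and does not inflate the type I error. This stands: it is a secondary defect and would not be serious alone.

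The protocol never names Lan-DeMets, so the classic pair 0.0052/0.0480 is another reading of O'Brien-Fleming, and a declared conservative split at 0.0469 would also control alpha. This too is fair. The printed 0.0031 nevertheless points to the spending-function version, for which 0.0490 is the companion.

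Finally, the 1-in-8 figure holds only if 30% v 10% is true, and {14} itself calls these assumptions uncertain. With smaller effects the chance of conflict falls to about 5% or 2%.

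**Conclusion.** The concern holds and must be fixed before the interim. The interim rule contradicts itself by a factor of ten. At the design assumptions, with 69 evaluable patients and an uncorrected chi-square test, 12-13% of trials would receive opposite instructions from the two sections. The share is smaller if the true effect is smaller.

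The final level 0.0469 does not match either printed interim value. It leaves overall alpha at 0.0480 (with 0.0031) or 0.0469 (with 0.00031) instead of 5%, and costs about 0.2-0.5 points of power. This second part is conservative and minor; the severity rests on the interim contradiction. The boundary calculations assume information of exactly 50% and the usual normal approximation.

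**What to change.** State the same pair in {20a} and {21b}: at 69 evaluable patients, stop for efficacy if the two-sided chi-square p-value is below 0.0031 in favour of the experimental arm; at the final analysis, claim superiority if it is below 0.0490. Name the boundary as Lan-DeMets O'Brien-Fleming-type spending with overall two-sided alpha 0.05.

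Add that both levels will be recomputed from the spending function if the information fraction at the look is not 50%. For example, the pair is 0.0017/0.0494 at 45% and 0.0050/0.0484 at 55%.

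If the sponsor intended the classic boundary, the pair is 0.0052/0.0480. If 0.0469 is to stay as a deliberate conservative choice, the text should say so.

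The cost is one sentence in each of two sections, with no extra patients or data, provided it is done before anyone sees interim results.

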#### Secondary outcomes

The following secondary outcomes will be assessed up to 3 months after surgery:Neurological deficits evaluated by the modified Rankin scale (mRS)Quantity and characteristics of recurrence-associated complicationsQuantity and characteristics of complications associated with endovascular embolization

The mRS [36] measures the degree of disability or dependence in the daily activities of people who have suffered a stroke or other causes of neurological disability. Scale values and interpretations are:0 = No symptoms.1 = No significant disability. Able to carry out all usual activities, despite some symptoms.2 = Slight disability. Able to look after own affairs without assistance, but unable to carry out all previous activities.3 = Moderate disability. Requires some help, but able to walk unassisted.4 = Moderately severe disability. Unable to attend to own bodily needs without assistance, and unable to walk unassisted.5 = Severe disability. Requires constant nursing care and attention, bedridden, incontinent.6 = Dead

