**Assessments**						
Demographics, medical history, laboratory data			X			
Neurological tests			X		X	X
Computed tomography			X		X	X
Complications				X	X	X

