## Data collection and management

### Plans for assessment and collection of outcomes {18a}

Data will be entered by clinical investigators and supporting trial personnel on electronic case report forms (eCRFs) created by secuTrial®.

Neurological examination comprises the modified Rankin scale for neurologic disability [36], the muscle function according to Janda [37], the presence of word finding disorders, hemiparesis, and anisocoria, as well as vigilance. Standard laboratory parameters will be taken from peripheral blood at baseline and during follow-up. The size and extent of cSDH will be measured on non-contrast CT scans.

The following parameters of recurrence-associated or intervention-associated complications will be documented for study purposes:

Recurrence-associated:Cerebral edemaCerebral infarction

Intervention-associated:Dissection of vessels by the guide wireDislocation of particles or coilsIschemia caused by internal-external vascular connectionsRetinal blindnessEpidural hematoma after MMA perforationInflammation or abscess at the puncture siteVascular fistula at the puncture siteVascular bulging at the puncture siteAllergic reaction to the contrast agentAcute renal failure

Complications not covered by predefined categories may be entered as free text in the eCRF.

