### Methods for additional analyses (e.g., subgroup analyses) {20b}

Primary and secondary outcomes will be stratified for age in a categorial manner (i.e., ≤67 and >67 years, the common retirement age in Germany).

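### The test rule that in practice governs the mRS leaves the ordinal analysis unspecified and would send almost any seven-level table to a test that ignores order

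*Protocol article*

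**What the plan says.** All places are in the protocol article.

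- **Statistical methods for primary and secondary outcomes {20a}** gives one rule: "Secondary categorical outcomes will be investigated by the Cochran-Mantel-Haenszel (CMH), chi-square", or Fisher's "exact test (if one of the cell frequencies is <5"). The next sentence reports both kinds of complication, and adverse events, as absolute and relative frequencies.
- **Secondary outcomes** lists first "Neurological deficits evaluated by the modified Rankin scale (mRS"), followed by the two complication outcomes. It defines the scale from 0 (no symptoms) to 6 (dead): "The mRS [36] measures the degree of disability or dependence in the daily activities of people". It gives no cut-off or grouping and does not rank the three outcomes.
- **Plans for assessment and collection of outcomes {18a}**: "Neurological examination comprises the modified Rankin scale for neurologic disability".
- **Table 1** marks "Neurological tests" at baseline, 1 month and 3 months, so a baseline mRS will exist.
- **Methods for additional analyses {20b}** names age as the only stratification: "Primary and secondary outcomes will be stratified for age in a categorial manner", split at 67 years.

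**The concern.** The complication outcomes are descriptive, so mRS is the one listed secondary outcome that clearly needs the test sentence. Two of its three tests treat the levels as interchangeable labels. The third, CMH, can use order in its row-mean-score or correlation form, but neither form nor any scores are named. The cell-count condition then acts as a data-dependent switch, and a sparse seven-level table meets it almost automatically.

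An analyst who follows the sentence literally would therefore compare disability between arms with an unordered test. A genuine shift along the scale could be reported as no significant difference, in the only listed secondary outcome that measures function.

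**Working it through.** **Sample size available.** The article states no power, effect size or distribution for mRS. The number of patients comes from the primary outcome (30% vs 10%, two-sided 5%, power 80%):

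- Unpooled: n = (0.3×0.7 + 0.1×0.9)×7.849/0.2² = 58.87, where 7.849 = (1.960 + 0.842)².
- With continuity correction: (58.87/4)×[1 + √(1 + 4/(58.87×0.2))]² = 68.5, i.e. 69 per arm, 138 in total.
- Drop-out: 138/0.9 = 153.3, i.e. 154.

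This matches the article, so 69 per arm is used below.

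**Assumptions for mRS.** Percentages at levels 0 to 6 in the control arm:

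- A: 25/28/17/12/8/4/6
- B: 15/20/20/17/13/7/8
- C: 40/27/12/8/5/3/5

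The experimental arm is obtained by multiplying the cumulative odds c/(1−c) at every level by a common odds ratio (OR).

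**Does the cell rule trigger?** A level needs 5/69 = 7.2% of an arm merely to have an expected count of 5. Take B, the flattest case, at OR 2.0. Levels 0-5 hold 0.92 of controls, with odds 0.92/0.08 = 11.5. Doubled, this is 23, so level 6 holds 1/24 = 4.2%, or 2.9 patients. In simulation at least one cell fell below 5 in 91% of trials (B, no effect) and in 99-100% of all other scenarios.

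**Power.** 2,000 simulated trials per row, two-sided 5%; the Monte Carlo standard error is at most √(0.5×0.5/2000) = 1.1 points. The ordinal test is the Wilcoxon test, equivalent to CMH row-mean-score with rank scores. Fisher's test is its 2×7 extension (Fisher-Freeman-Halton), by Monte Carlo.

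| Distribution, OR | Chi-square, 6 df | Fisher 2×7 | Ordinal, 1 df | mRS 0-2 vs 3-6 |
|---|---|---|---|---|
| A, 1.8 | 22.4% | 23.9% | 46.3% | 30.3% |
| B, 1.8 | 25.1% | 26.3% | 51.4% | 37.7% |
| C, 1.8 | 21.6% | 25.3% | 46.9% | 24.8% |
| A, 2.0 | 32.7% | 34.9% | 60.7% | 41.1% |
| B, 2.0 | 33.8% | 34.9% | 64.6% | 49.7% |
| C, 2.0 | 28.1% | 31.0% | 58.3% | 30.5% |
| A, 2.4 | 52.3% | 55.0% | 82.8% | 58.7% |
| B, 2.4 | 52.8% | 53.5% | 82.2% | 67.6% |
| C, 2.4 | 46.0% | 51.4% | 77.2% | 44.0% |

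- Ordinal minus chi-square: from 46.3 − 22.4 = 23.9 to 77.2 − 46.0 = 31.2 points.
- Ordinal minus Fisher: from 46.9 − 25.3 = 21.6 to 64.6 − 34.9 = 29.7 points.
- Fisher minus chi-square: 0.7 to 5.4 points in Fisher's favour, so the switch itself costs no power.
- Ordinal minus dichotomised: from 51.4 − 37.7 = 13.7 to 77.2 − 44.0 = 33.2 points.

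A separate simulation, also with three assumed distributions, gave at OR 2.0 30-32% (chi-square), 58-61% (ordinal) and 36-50% (dichotomised). All lie within the ranges above.

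**Mechanism.** With noncentrality 7.849, a 1-df test has 80% power and a 6-df test 52%.

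**Baseline mRS.** Let r be the correlation between baseline and 3-month value. Approximate adjusted power is Φ(d/√(1−r²) − 1.960), with d = z(unadjusted power) + 1.960. From 61% unadjusted, d = 0.279 + 1.960 = 2.239. This gives 65% (r = 0.3), 73% (r = 0.5) and 80% (r = 0.6). The correlations are assumptions.

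**The case against.** The strongest reply is that the article fixes less than a reader might infer.

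- **Unordered tests are not prescribed for mRS.** CMH is named first. Its row-mean-score form is ordinal, has about Wilcoxon power and fits the age stratification in {20b}. This stands: the text leaves the choice open. However, it does not name that form, and the cell-count condition pulls a sparse table towards Fisher's test.
- **A seven-level comparison is not stated.** On a dichotomised mRS, chi-square and Fisher are suitable and the cell rule need not trigger. This also stands. But no cut-off is given, the 0-2 versus 3-6 split had less power than the ordinal test in every row of the table, and an unfixed cut-off could be chosen after seeing the data.
- **Fisher's test is not the cause of the loss.** It is tempting to blame the below-5 rule. The table shows Fisher level with or slightly above chi-square.
- **mRS is not called the main secondary outcome.** It is only listed first, and no power was promised for it.
- **Covariates and scoring are commonly left to the SAP.** This is fair, and the absence of baseline adjustment would not be a finding on its own. The point rests on the test rule that the article does state, which a SAP following it would inherit.

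**Conclusion.** The concern holds in limited form. The stated rule does not secure an ordinal analysis of an ordered scale, and applied literally to seven levels it would select an unordered test in nearly every trial of this size. Ignoring order would then cost about 24-31 points of power with chi-square, or 22-30 with Fisher's test, at common odds ratios of 1.8-2.4. At OR 2.0 a real shift would be missed about two times in three, against roughly two in five with an ordinal test.

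These sizes depend on assumed mRS distributions and a proportional-odds shift, since the article gives neither. The gap was similar across all three distributions. The documents do not support saying that the plan commits to an unordered analysis or rules out baseline adjustment. The unused baseline value is a supporting point whose gain depends on an unknown correlation. The primary analysis is unaffected.

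**What to change.** State in {20a} that mRS at 3 months is analysed on its full scale by proportional-odds regression with arm, baseline mRS and the randomisation stratification factors, reporting a common odds ratio with 95% CI. Say that deaths count as level 6, because {11b} lists death among the drop-out criteria. Add an age-stratified CMH row-mean-score (van Elteren) test as a check, and restrict chi-square and Fisher's test to binary secondary outcomes.

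The cost is a few sentences; every variable is already scheduled for collection. The one drawback is reliance on the proportional-odds assumption, which the rank-based check covers. The change should be made before any outcome data are compared by arm, so that the choice cannot depend on them.

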**Methods:**

MEMBRANE is an investigator-initiated, single-center, randomized controlled trial. Male, female, and diverse patients older than 18 years scheduled for surgical evacuation of a first cSDH will be assigned in a 1:1 fashion by block randomization to the intervention (surgery plus endovascular MMA embolization) or the control group (surgery alone). The primary trial endpoint is cSDH recurrence within 3 months of follow-up after surgery. Secondary endpoints comprise neurological deficits assessed by the modified Rankin Scale (mRS) and recurrence- or intervention-associated complications during 3 months of follow-up. Assuming a risk difference of 20% of rebleeding and surgical revision, a power of 80%, and a drop-out rate of 10%, 154 patients will be enrolled onto this trial, employing an adaptive O’Brien-Fleming approach with a planned interim analysis halfway.

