### Trial design {8}

MEMBRANE is an investigator-initiated, single-center, randomized controlled trial testing whether neurosurgical hematoma evacuation plus endovascular embolization of the MMA (intervention group) is superior to surgery alone (control group) in reducing the recurrence rate of cSDH within a follow-up period of 3 months. Eligible patients will be allocated in a 1:1 ratio to either the intervention or control group (see study flowchart in Fig. 1).

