### Adverse event reporting and harms {22}

All SAEs reported by study participants or observed by an investigator within the study period must be documented in the eCRF. SAEs are any undesirable sign, symptom, or medical condition whichIs fatalIs acutely life-threateningRequires or prolongs inpatient hospitalizationResults in persistent or significant disability/incapacityConstitutes a congenital anomaly or birth defect (not applicable, pregnancy excludes from study participation)

The principal investigator will be informed immediately about the onset of a SAE and must decide whether the participant shall be excluded from or remain in the study. The likelihood of a causal relationship between the individual trial intervention and SAE will be investigated further, and patients will be observed until the SAE resolves or a stable condition is reached.

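### A recurrence that needs surgery is also an SAE, so an undivided SAE total by arm partly repeats the primary endpoint and could mask an excess of other serious events

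*Protocol article*

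**What the plan says.** Four parts of the protocol article bear on this point.

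- **Primary outcome (Outcomes {12}).** Recurrence within 3 months counts if the haematoma returns to about its baseline volume or more, if it needs surgery, or both.
- **SAE definition (Adverse event reporting and harms {22}).** An event that leads to or lengthens a hospital stay is serious. The capture rule is unrestricted: "All SAEs reported by study participants or observed by an investigator within the study period must be documented in the eCRF". Endpoint events are not exempted. The same section requires the likely causal link between intervention and SAE to be investigated.
- **Safety analysis (Statistical methods for primary and secondary outcomes {20a}).** The sentence opens with two separate categories, "Recurrence-associated complications, complications associated with endovascular embolization", and ends "serious) adverse events will be expressed as absolute and relative frequencies". It does not separate SAEs that are recurrences from other SAEs.
- **Complication lists (Plans for assessment and collection of outcomes {18a}).** The predefined recurrence-associated items are cerebral edema and cerebral infarction. Ten intervention-associated items are predefined, and other complications can be entered as free text.

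**The concern.** A patient who returns for repeat evacuation of a recurrent haematoma has reached the primary endpoint and, in practice, has also met the hospitalization criterion for an SAE. The recurrence-associated category does not remove that event from the SAE count, since neither the recurrence nor the re-operation is among its predefined items.

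If embolization lowers recurrence as assumed, total SAEs will tend to be lower in that arm for that reason alone. The trial aims to assess safety as well as effectiveness, and its Discussion speaks of weighing benefit against risk. Of the frequencies listed in {20a}, the SAE frequency is the one that can compare arms without first judging cause. If it also contains the efficacy effect, a reader could count one benefit twice and miss an excess of other serious events that offsets it.

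**Working it through.** **Inputs from the protocol.** Sample size {14} assumes "recurrence rates of 30% in the control and 10% in the experimental arm" and 69 evaluable patients per group. The Abstract describes the same difference in these words: "Assuming a risk difference of 20% of rebleeding and surgical revision". The enrolment figure reproduces: 138 / 0.90 = 153.3, rounded up to 154, or 77 per arm. Below, 69 serves only as a multiplier.

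**Inputs not in the protocol, so assumed and varied.** The protocol gives no SAE rate and no share of recurrences that are re-operated. Let

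- f = share of recurrences that need surgery;
- q = control-arm risk of any other SAE;
- h = added risk of serious harm from embolization;
- k = ratio of other-SAE risk, embolization to control.

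Recurrence and other SAEs are taken as independent.

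**Step 1: how much of the endpoint enters the SAE count.** With f = 1, the expected numbers are 0.30 × 69 = 20.7 in control and 0.10 × 69 = 6.9 with embolization, or about 21 and 7 patients.

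**Step 2: illustration with f = 1, q = 10%, h = 10%.**

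- Other SAEs: control 10%; embolization 1 − 0.90 × 0.90 = 19%, so k = 1.9.
- Any SAE, control: 1 − 0.70 × 0.90 = 37.0%.
- Any SAE, embolization: 1 − 0.90 × 0.90 × 0.90 = 27.1%.

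The total favours embolization by 9.9 points, while other SAEs are 9 points worse.

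**Step 3: added harm at which the totals become equal.** Setting the two any-SAE risks equal gives h = 1 − (1 − 0.3f)/(1 − 0.1f), which does not depend on q.

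- f = 1: 1 − 0.70/0.90 = 22.2%.
- f = 0.5: 1 − 0.85/0.95 = 10.5%.

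**Step 4: vary the background rate, with f = 1 and k = 1.9.**

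| Other SAEs, control | Other SAEs, embolization | Any SAE, control | Any SAE, embolization |
|---|---|---|---|
| 5% | 9.5% | 33.50% | 18.55% |
| 10% | 19% | 37.00% | 27.10% |
| 15% | 28.5% | 40.50% | 35.65% |
| 20% | 38% | 44.00% | 44.20% |

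**Step 5: where the reversal ends.** Solving (1 − 0.3f)(1 − q) = (1 − 0.1f)(1 − kq) for q gives q = 0.2f / [(1 − 0.1f)k − (1 − 0.3f)]. With k = 1.9:

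- f = 1: 0.20 / (1.71 − 0.70) = 19.8%.
- f = 0.5: 0.10 / (1.805 − 0.85) = 10.5%.
- f = 0.25: 0.05 / (1.8525 − 0.925) = 5.4%.

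Above these rates the total also shows embolization as worse, so the direction is no longer reversed.

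**The case against.** **Recognised procedural harm has its own route.** Embolization complications are a secondary objective and a secondary outcome, with ten predefined items plus free text. They are recorded at embolization and at both follow-ups, and reported apart from SAEs. SAE causality is investigated, and the mRS, which scores death as 6, offers another route for disabling or fatal harm. This largely stands. A reader might infer that the plan will hide the serious harm embolization causes; the documents do not support that. What stays exposed is mainly serious harm not recognised as embolization-related.

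**The plan names no any-SAE composite.** Section {20a} does not define patients with any SAE as a measure, does not test SAEs between arms and does not write that they are shown by arm. If they were listed by event type, recurrence would have its own line. This stands as a limit: the point concerns a total by arm, which is a natural summary in a two-arm trial but not a specified one.

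**The size is assumed.** The 10% background rate, the 10% added harm and full re-operation are not in the protocol, whose own account of the procedure is more favourable. Volume-only recurrences need not be SAEs. The Abstract's mention of surgical revision points to a high re-operated share but does not fix it. This stands too, which is why ranges are shown.

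**Table layout belongs to the SAP, and the split can be made later.** This is partly right. Recurrence and SAEs are both recorded per patient. But the SAE definition and its summary are set in this document and overlap as written. Deciding afterwards which SAEs were the endpoint is avoidable judgement in a trial whose treating investigators are not blinded.

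**Re-operation is a real burden.** Agreed. A total that includes it describes net burden and should stay.

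**Conclusion.** The overlap follows from the protocol's own definitions: the SAE count contains the surgical part of the primary endpoint, and {20a} does not separate it. A total SAE comparison by arm would partly restate the efficacy result in favour of embolization.

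How far this could mask other serious events is conditional. The 37.0% versus 27.1% contrast, against 10% versus 19% for other SAEs, rests on independence and on assumed rates. A near-doubling reverses direction only while the control-arm rate of other SAEs is below about 20%, 10.5% or 5%, for all, half or a quarter of recurrences re-operated. A reader might infer that a near-doubling would generally go unseen, or that a total including recurrences is invalid. Neither follows: the first depends on rates the protocol does not give, and the second overlooks that the total is a legitimate measure of burden.

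The primary test, sample size and error rates are unaffected. This is a modest improvement in safety reporting.

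**What to change.** 1. In Statistical methods {20a}, report SAEs by arm in two lines shown side by side: (a) all SAEs, and (b) SAEs excluding recurrent cSDH and the re-operation for it. Complications of a re-operation stay in (b). Neither line needs to be named the sole safety summary.
2. In Adverse event reporting and harms {22}, add an eCRF flag for an SAE that is itself the primary-endpoint event.

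SAE reporting duties stay unchanged. The cost is one flag and one extra table line, with no added patients or assessments. If an SAP not shown here already makes this split, only the flag remains to be added.
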